## Abstract

**Background:**

Low back pain (LBP) is a major health problem in modern society, with 70-85% of the population experiencing LBP at some time in their lives. Each year, 5-10% of the workforce misses work due to LBP, most for less than 7 days. Almost 10% of all patients are at risk of developing chronic pain and disability. Little clinical evidence is available for the majority of treatments used in LBP therapy. However, moderate evidence exists for interdisciplinary rehabilitation, exercise, acupuncture, spinal manipulation, and cognitive behavioral therapy for subacute and chronic LBP. The SMATH^® ^system (system for automatic thermomechanic massage in health) is a new medical device (MD) that combines basic principles of mechanical massage, thermotherapy, acupressure, infrared therapy, and moxibustion. SMATH^® ^is suitable for automatic multidisciplinary treatment on patients with non-specific sub-acute and chronic LBP.

**Methods/design:**

This paper describes the protocol for a double-blinded, sham-controlled, randomized, single-center short term clinical trial in patients with non-specific sub-acute and chronic LBP aged 18 to 70 years. The primary outcome will be the effectiveness of SMATH^® ^versus sham therapy (medical device without active principles) determined by evaluating self perceived physical function with Roland Morris Disability Questionnaire (RMDQ) scores after 4 weeks of treatment (end of treatment). Major secondary outcome will be effectiveness of SMATH^® ^determined by evaluating self perceived physical function comparing RMDQ scores between end of treatment and baseline. The trial part of the study will take 7 months while observational follow-up will take 11 months. The sample size will be 72 participants (36 for each arm). The project has been approved by the Ethical Committee of Cremona Hospital, Italy on 29 November 2010.

**Discussion:**

Compared to other medical specialties, physical and rehabilitation medicine (PRM) has not yet received the deserved recognition from clinicians and researchers in the scientific community, especially for medical devices. The best way to change this disadvantage is through well-conducted clinical research in sham-controlled randomized trials. Sham treatment groups are essential for improving the level of evidence-based practice in PRM. The present trial will counter the general lack of evidence concerning medical devices used in LBP therapy.

**Trial Registration:**

ISRCTN: ISRCTN08714168

## Background

Low back pain (LBP) is a major health problem in modern society; 70-85% of the population will experience LBP at some time in their lives [1]. Each year, 5-10% of the workforce misses work due to LBP, the majority for less than 7 days [2]. Almost 10% of all patients are at risk of developing chronic pain and disability, accounting for more than 90% of the costs associated with back-related disability [3]. LBP incurs substantial treatment and productivity costs worldwide [4]. Healthcare and social costs for LBP are increasing rapidly. In the United States, healthcare costs among people with LBP increased 65% between 1997 and 2005, more rapidly than overall healthcare costs [5]. In the United States, chronic LBP is estimated to cost Americans over 70 billion dollars per year in health care expenditures [6]. The total cost of treatment, lost work days, and disability due to chronic pain in 1995 and 1996 was estimated to be between 150 and 215 billion dollars [7]. In the UK, 1.3 million people receive physiotherapy for LBP each year, with a global cost of £150 million for the National Health System (NHS) [8]. In Italy, the global economic impact of LBP is approximately €24 billion per year, and patients pay almost all fees.

LBP has been difficult to treat solely using medical interventions due to the complex interplay of biological, psychological, and social factors in its onset and persistence. LBP is usually a benign and self-limiting condition, but many patients look for some type of therapy to relieve their symptoms and provide hope for a cure. For this reason, more than 50 potential therapies promise to relieve the pain [2,9], lessen the suffering, and offer a cure for this problem. However, sound evidence exists for a small number of these therapies [9]. For the interventions with multiple reviews, conflicting conclusions have been reached about effectiveness due to the heterogeneity and poor quality of the trials, but there are more qualitative systematic reviews than meta-analyses, and two-thirds of systematic review authors emphasize that more high quality trials are needed [10]. Despite advances in knowledge, technology, and procedures, no medical treatment has been demonstrated to consistently and completely alleviate LBP. Clinical evidence for the majority of treatments used in LBP therapy is also inconsistent. However, moderate evidence exists for interdisciplinary rehabilitation, exercise, acupuncture, spinal manipulation, and cognitive behavioral therapy for sub-acute and chronic LBP [5,11]. In particular, multidisciplinary interventions seem to be the most promising approach for patients with sub-acute and chronic LBP [12]. Intensive multidisciplinary biopsychosocial rehabilitation with a functional restoration approach has been shown to reduce pain and improve function in patients with chronic LBP [13]. In addition, empirical evidence has shown the sort of information and advice that should be given to patients with back pain, confirming that such information and advice may be a potent element of the health care intervention [14]. Soft-tissue massage is thought to improve physiological and clinical outcomes by offering symptomatic pain relief through physical and mental relaxation and increasing the pain threshold via the release of endorphins [2,15]. The gate-control theory predicts that massaging a particular area stimulates large diameter nerve fibers. These fibers have an inhibitory electrical input to T cells, which are the first cells to project into the central nervous system within the spinal cord [2]. T-cell activity is likely depressed, whereas small diameter nerve fibers (nociceptive fibers) have an excitatory input, and pain relief follows [16]. Massage therapy may provide benefits by shifting the autonomic nervous system from a state of sympathetic response to a state of parasympathetic response. Massage is similar or superior to other conservative therapies, such as exercises, mobilization, relaxation, physical therapy, acupuncture, and self-care education [2]. Massage is beneficial for patients with sub-acute and chronic nonspecific LBP in terms of improving symptoms and function, but the benefits of massage increase when combined with exercises and education [2]. Massage has powerful analgesic effects if applied to acupuncture points, a technique known as "acupressure" [2]. Two studies that compared massage to inert treatment (sham therapies) showed that massage is superior for pain and function in both short and long-term follow-up [17,18]. No serious adverse events were reported by any patient in the studies reviewed [2]. Massage alone is unlikely to be cost-effective [5]. Focusing on high-quality randomized controlled trials (RCTs) with a sufficient sample size to draw firm conclusions is particularly recommended for future research involving LBP therapies [12].

## Trial Rationale

SMATH^® ^is a new medical device that combines basic principles of mechanical massage, thermotherapy, acupressure, infrared therapy, and moxibustion. SMATH^® ^is included in the "conservative treatments" category [13]. This device is capable of releasing modulated and controlled thermomechanic energy on the patient following a programmable and fully reproducible automatic treatment program selected by the operator. Energy (thermomechanic and infrared) is released at the same time under the spine and legs of the patient. We think this system provides a true automatic multidisciplinary treatment for patients with sub-acute and chronic LBP. The SMATH^® ^system should theoretically be capable of combining the single clinical benefits of massage, thermotherapy, infrared, and acupressure, removing the dependency on operator capability, though obviously missing some elements of human touch, and providing maximum automaticity and reproducibility and producing a real clinical added value for patients. The literature involving different reviews show that little clinical evidence exists on the use of these endorsed therapies on their own. In particular, there is little evidence for massage performed by hands or a mechanical device, or and for superficial heat release [12]. No evidence is available for thermotherapy [13], or for moxibustion, infrared therapy, and acupressure. On the other hand, moderate evidence indicates the effectiveness of multidisciplinary treatment compared to other kinds of active treatment in regards to pain intensity at short-term follow-up [12]. The SMATH^® ^system was developed in an attempt to create an effectiveness advantage by combining different basic theoretical principles. The first clinical results, from the safety clinical study involving 46 patients inside the process to obtain the European Conformity (CE) mark for SMATH^®^, showed the following: RMDQ average score of 10.96 (sd = 3.04; p < 0.05) at baseline and 3.21 (sd = 2.99; p < 0.05) after 3 months, and the average quality adjusted life year (QALY) was 0.46 (sd = 0.13; p < 0.05) at baseline and 0.81 (sd = 0.12; p < 0.05) after 3 months. These data have not been published because they were not suitable for publication and represented the results obtained by one clinical study in which the primary outcome was the demonstration of clinical safety. The internal clinical report concerning this study has been delivered to the notified body in charge of the CE mark process. The SMATH^® ^system obtained the CE mark on 20 December 2010. The current RCT was designed to investigate and test the SMATH^® ^system for use in LBP therapy.

The cost/effectiveness ratio for the SMATH^® ^system may also be interesting and could play an important role in the Italian NHS strategy for LBP interventions. An HTA procedure has already been launched in Italy for this new therapy. Like all new technologies and interventions, the clinical effectiveness of the SMATH^® ^system has to be proven by clinical studies in a PRM context. Compared to other medical specialties, PRM has not yet received the recognition deserved from clinicians and researchers in the scientific community, especially for medical devices [19]. We think this unfavorable scenario is due to several reasons, one of which is the lack of high-quality clinical trials in the PRM field. Conducting double-blind placebo-controlled trials in the specialty is difficult; the majority of studies in PRM are practically based on clinical observation, uncontrolled observational studies, or clinical trials comparing two different active therapies. Consequently, these studies are not suitable for providing sufficient proof of efficacy for these therapeutic modalities. The only scientifically recognized way to achieve this goal is to design and manage high-quality double-blind placebo-controlled trials. Sham treatment groups in clinical trials are essential for improving the level of evidence-based practice in PRM. This trial was conceived to reduce the lack of evidence and quality for LBP therapy. No major and minor adverse events or adverse effects have been observed during the use SMATH^® ^on patients with LBP. The SMATH^® ^system has the CE mark as it has passed all tests concerning safety for the patient, operators, and environment. For this reason, no adverse events are expected during this clinical study. However, if adverse events occur, they will be reported to the regulatory authority and ethics committee in accordance with applicable regulations. Trial results will be used to inform HTA procedure already involving SMATH^® ^therapy for health care policies regarding the treatment of LBP in Italy.

## Methods

### Design

This is a double-blinded, sham-controlled, randomized, single-center short term clinical trial involving 72 participants. Thirty-six participants will be treated with SMATH^® ^therapy and compared to 36 participants treated with sham therapy (same medical device without active principles). All participants are patients with non-specific sub-acute and chronic LBP, aged 18 to 70 years. Exclusion criteria verification will be done at baseline (T1) with the identification of eligible participants. One week after T1 (T2), eligible participants who have signed informed consent and satisfy the inclusion criteria will be randomized into either the SMATH^® ^or sham groups. Participants who are not randomized will be submitted to the most suitable therapy by the investigators and sent to TF1 to enter in the observational follow-up. Randomized participants will attend clinic visits at T2 (one week after T1), T3 (two weeks after T2) and T4 (two weeks after T3). The design of the clinical trial is depicted in Figure 1. At T4, treatments will be complete and all participants can continue the most suitable therapy, as indicated by the investigators, and enter the long-term observational follow-up phase, which will last 11 months. All participants will be followed starting at TF1 (same time as T4,) for 11 months and will attend clinic visits at 1 month (TF2), 4 months (TF3), 7 months (TF4), and 11 months (TF5) after TF1. The design of the observational follow-up period is depicted in Figure 2.

**Figure 1 F1:**
[figure not shown]
**Clinical Study Design**.

**Figure 2 F2:**
[figure not shown]
**Follow-up Design**.

### Eligibility

Subjects with sub-acute and chronic non-specific LBP diagnosed according to generally accepted scientific criteria [13] were enrolled. Inclusion criteria were as follows: aged between 18 and 70 years, ability to sign informed consent, ability to complete the study, ability to complete the questionnaires, RMDQ score ≥ 4 at T2 [20], and negative answers on all exclusion questions at T1. The rationale for the inclusion criteria is provided in Table 1.

**Table 1 T1:** Rationale for Inclusion Criteria

Inclusion criteria	Rationale
Age between 18 and 70 years	This age interval was chosen in accordance with actual main reviews in PRM [2,10,12]

Ability to sign informed consent	Mandatory for participant inclusion in clinical studies (Helsinki Declaration article 22)

Ability to complete the study	To prevent drop-outs

Ability to complete the questionnaire	Mandatory for accurate data collection

RMDQ score ≥ 4 at T2	From the literature [20]

Negative answers for all exclusion criteria	This check performed at T2 confirms that the exclusion evaluation was performed at T1.

Exclusion criteria were as follows: pregnancy (real or suspected) or breast-feeding; receiving physical therapy treatments in the 15 days preceding T1; treatment with cortisone in the month preceding T1, implanted with pacemaker or implantable cardioverter defibrillators (ICD) or, more generally, a user of active implantable devices; use of medullar stimulators and infusion pumps; recent or ongoing deep venous thrombosis (DVT); use of spine stabilization devices; serious osteoporosis associated with bone fracture risk, including soft or acutely infected bone tissues; acute cardiovascular disease; neoplastic disease; systemic rheumatic disease; or traumatic spinal episodes in the 3 months preceding T1. The rationale for the exclusion criteria is provided in Table 2.

**Table 2 T2:** Rationale for exclusion criteria

Exclusion criteria	Rationale
Pregnancy (real or suspected) and breast-feeding	These patients have a risk of some alteration due to the mechanical and thermal energy release

Subjects who received physical therapy treatments in the 15 days preceding T1	These treatments could influence the results of the study

Subjects treated with cortisone in the month preceding T1	This treatment could influence the results of the study

Subjects implanted with pacemakers and ICDs (implantable cardioverter defibrillators); more generally, users of active implantable devices	In order to prevent possible electromagnetic interference between SMATH^® ^and the implantable device, which is potentially dangerous for the patient (cautelative criteria)

Subjects with medullar stimulators and infusion pumps with recent or ongoing DVT (deep venous thrombosis)	To prevent possible electromagnetic and mechanical interference between SMATH^® ^and the implantable device, which is potentially dangerous for the patient (cautelative criteria)

Subjects with spine stabilization devices	These treatments could influence the results of the study

Subjects with serious osteoporosis associated with bone fracture risk	Mechanical energy release on these patients could increase bone fracture risk

Subjects with logically soft or acute infection of bone tissues	Thermal and mechanical energy release could increase infection diffusion

Subjects with acute cardiovascular disease	These patients need to be submitted to specific clinical evaluation before being treated for LBP

Subjects with neoplastic disease	These patients need to be submitted to specific clinical evaluation before being treated for LBP

Subjects with systemic rheumatic disease	These patients need to be submitted to specific clinical evaluation before being treated for LBP.

Subjects with traumatic spinal episodes the 3 months preceding T1	Mechanical energy release on these patients could be dangerous.

### Setting and locations where the data will be collected

A special area inside the Head Investigator's office in the Hospital will be dedicated to data collection and storage. Case report forms (CRFs) for the enrolled subjects will be kept strictly inside this area. Treatment plan sheets on which the treatment plan for each randomized participant will be recorded will be delivered externally by the technician in charge of executing the treatment. Before randomization, randomization envelopes will be held in this area by the Head Investigator and remain sealed, even after delivery, until used by the technician in charge of administering the treatment. Access to the CRFs by the investigators and monitor will be authorized by the Head Investigator. The technicians in charge of administering treatment will be responsible for storing the envelopes and treatment plan after randomization and treatment plan; they will have to practice maximum confidentiality about their contents as investigators will not have access to this information.

### Randomization

A simple randomization process has been conceived through three different steps according to the Consolidated Standards of Reporting Trials (CONSORT) statement: sequence generation, allocation concealment, and implementation.

**Sequence generation **has been achieved through a "congruential multiplier" statistical algorithm application, using IBM Statistical Package for Social Sciences (SPSS) Version 19 [21,22] and was stratified with 1:1 allocation random block size of 36. The randomization list reports a progressive randomization number for randomized participants (from 1 to 72), and the treatment (A or B) will be assigned for each of them.

For **allocation concealment**, the randomization list was produced in three numbered copies. The first copy was delivered to the Ethics Committee inside an envelope sealed with warm sealing wax. A second copy was delivered to the Head Investigator in a similar sealed envelope. The Head Investigator will save his copy in a locked box in his office. He can open the envelope in the case an emergency arises. A third copy has been kept by the monitor of the study who managed the sequence generation. The monitor also prepared 72 opaque red envelopes containing randomization sheets. On each envelope is a number (from 1 to 72) and space for the patient's name and date of birth. The randomization sheet (opaque red) reports the progressive randomization number and assigned treatment (A or B) based on the randomization list. All of the envelopes have been closed and sealed with warm sealing wax. The 72 randomization envelopes were delivered to the Head Investigator, who will keep them in a locked box in his office. At the time of randomization, the investigator who decides to randomize the participant will take the first of the envelopes from the box in order of sequence and write the participant's name and date of birth on the envelope (to prevent subversion of the allocation sequence as suggested by Consort 2010, Item 9). Immediately after, the investigator will deliver the closed envelope and intervention plan to the technician in charge of administering the treatment. The technician will open the envelope to start the intervention, saving the envelope and randomization sheet in a locked box. The technicians involved in this phase of the study have been trained and educated to maintain maximum confidentiality concerning allocation concealment. This method will provide double-blinded conditions. Clinical investigators who enroll and evaluate participants will not know which treatment has been assigned to them.

**Implementation **of the randomization process will conform with the study requirements and steps described above. The process involves participant eligibility analysis, obtaining patient information, enrollment, treatment assignment, and data analysis to avoid any kind of bias. The implementation process is depicted in Figure 3.

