### Interventions for each group

Participants assigned to the SMATH^® ^therapy group (A arm) will have 14 treatment sessions of 45 minutes over 4 weeks starting at T2. The treatment module is associated with a dedicated educational booklet for each patient that provides general and behavioral indications for preventing LBP. In this clinical study, the educational booklet will be delivered to all enrolled participants to help them correct their lifestyle during and after the intervention period. In this dedicated booklet, different sections explain to the participants spine anatomy, LBP, LBP prevention, advantages of physical activity, suggestions for positions for walking, sleeping, and to keep weight under control, and exercises to prevent LBP.

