### Statistics and quality

The accuracy and completeness of the collected and registered data will be checked daily by clinical investigators to provide a suitable level of quality for the study. The external monitor will be responsible for arranging random periodic tests of quality throughout the study. In particular, controls will involve the quality and completeness of the CRFs, the treatment execution modalities, the drop-out rate, and correct respect of enrollment criteria application. Data analysis will be conducted using IBMSPSS 19 [21,22]. The morphological and clinical status of participants will be analyzed statistically. Motion functionality, level of pain perception, and quality of life will be evaluated through statistical analysis of the questionnaire scores. Short-term results will be evaluated to elaborate VAS and RMDQ scores, and medium and long-term results will be evaluated by EQ-5D scores, which will also be used to calculate the QALY and incremental cost effectiveness ratio (ICER) index [5,22], which is the most used and suitable index for analyzing the cost/effectiveness of PRM therapies [5]. Pain perception measured by VAS in the different phases and its severity analysis will be evaluated by analysis of variance using SPSS 19. Event incidence (SMATH^® ^versus sham) will be estimated using Kaplan-Meier curves, which will be compared using the log-rank test. Multivariable analysis will be performed using the Cox model.

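### The only emergency code break described opens the full 72-number list to the Head Investigator, who also holds the unused envelopes

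*Protocol article*

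**What the plan says.** The Randomization section describes both the list and its custody.

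- Content of the list: "The randomization list reports a progressive randomization number for randomized participants (from 1 to 72), and the treatment (A or B) will be assigned", one letter per number.
- Copies: "the randomization list was produced in three numbered copies". One went under seal to the Ethics Committee. For the next, "A second copy was delivered to the Head Investigator in a similar sealed envelope", which he keeps locked in his office.
- Emergency: "He can open the envelope in the case an emergency arises".
- Individual envelopes: 72 sealed, numbered envelopes, each holding one participant's sheet, are also kept by the Head Investigator in a locked box in his office. At randomization the investigator picks the next one in numerical order, marks it with the name and birth date of the person being randomized, and hands it closed to the technician. The technician opens it and locks away the envelope and sheet.
- Blinding: the same section says that the clinical investigators who enrol and assess participants are unaware of allocation. The section on setting and data collection adds that investigators have no access to what the technicians store.

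The section on interventions decodes the letter: "Participants assigned to the SMATH^® ^therapy group (A arm) will have 14 treatment sessions of 45 minutes".

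**The concern.** A code break should release one participant's allocation and nothing more. The route described releases a document covering the whole trial, and releases it to the person who keeps the envelopes not yet used.

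Two things would be at stake after an opening. The first is allocation concealment. According to the Design and Randomization sections, an investigator decides at T2 whether a participant is randomized, and those not randomized go to other therapy and the observational follow-up. If the next allocation is known, that decision can be influenced. The second is blinding to allocations already made. Investigators indicate therapy after T4, so knowledge of past allocations could affect care during the 11-month follow-up.

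Neither loss can be undone once the list has been read.

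**Working it through.** **Which envelope is meant.** In the Randomization section, the permission to open follows directly on the sentences about the Head Investigator's copy of the list. The 72 individual envelopes are introduced only afterwards. The envelope he may open is therefore the one with the full list.

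**How many allocations the list holds.** The section on sample size gives n = 26 per arm and a drop-out rate of 0.15. The article's own formula gives 26 / (1 − 0.15)² = 26 × 1.3841 = 35.99, rounded to 36 per arm, so 2 × 36 = 72. This matches the numbering of the list from 1 to 72.

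**Whether the letters A and B protect anything.** They do not. The section on interventions names SMATH as the A arm, so B is sham.

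**Whether numbers can be linked to people.** The list carries numbers, not names. For past participants, the envelopes are taken in numerical order and the participant's name is written on the numbered envelope, so the order of randomization gives the number. For the next participant, the number is that of the first envelope left in the box.

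**How much is disclosed.** Suppose the list is opened after k randomizations, for one of those k participants.

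- Needed: 1
- Surplus past allocations: k − 1
- Future allocations: 72 − k
- Total surplus: (k − 1) + (72 − k) = 71, whatever the value of k

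| k | Surplus past | Future | Total surplus |
|---|---|---|---|
| 1 | 0 | 71 | 71 |
| 10 | 9 | 62 | 71 |
| 36 | 35 | 36 | 71 |
| 60 | 59 | 12 | 71 |
| 72 | 71 | 0 | 71 |

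Opening one participant's sheet would give a surplus of 0 at every k. The threat to concealment is greatest early in recruitment and disappears once all 72 are randomized. The surplus of past allocations grows in the opposite direction.

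**Whether another route is described.** The individual sheets exist and are stored by the technician, but the article does not name them as a source for an emergency, and it states that investigators have no access to them.

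**The case against.** The strongest reply is that the harm is contingent. The article permits an opening but does not require one, and the Trial Rationale reports no adverse events with the device so far and expects none. If no emergency occurs, nothing is disclosed. This stands, and it limits the likelihood. The count of 71 measures exposure and is not an estimate of bias. Still, the article itself provides for an emergency, so the procedure should work when it is used.

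Second, the primary outcome is the participant's own RMDQ score, and participants would not be unblinded by the opening. This stands for outcome assessment. It does not cover selection into the trial or care during follow-up.

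Third, an article condenses a fuller protocol, and the additional file on adverse events and the figure on randomization are not shown. A route limited to one participant may exist there. The point, however, is about an arrangement that the article states outright, not about missing detail.

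Two stronger readings are tempting and are not supported:

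- A reader might infer that one opening ends blinding for all investigators. It unblinds one person. The article does not say that the Head Investigator enrols or evaluates participants, so wider loss depends on his role or on his passing the information on.
- A reader might also infer a leak through the monitor: "A third copy has been kept by the monitor of the study who managed the sequence generation", and an external monitor later checks case report forms and drop-out. The article does not say whether that copy is open or sealed, nor that the monitor enrols or assesses anyone. Sealing the paper would in any case not remove what the person who generated the list already knows.

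**Conclusion.** The point holds as a weakness in a stated procedure. The single emergency route described discloses 72 allocations in place of 1, a surplus of 71, to the custodian of the unused envelopes.

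The reading of the text is secure. The consequences are conditional:

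- Concealment for the remaining 72 − k participants is put at risk only if an emergency opening takes place before recruitment ends.
- The statement that enrolling and evaluating investigators are blind fails for the Head Investigator only if he does one of those tasks.

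No sample-size figure is affected. The change is worth making because the loss would be irreversible and the means to avoid it are already in the trial.

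**What to change.** 1. Do not keep the full list with the Head Investigator.
2. State that in an emergency only the affected participant's own randomization sheet is disclosed, from the technician's locked box.
3. Add a matching exception to the statement, in the section on setting and data collection, that investigators have no access to the technicians' material.
4. Keep the Ethics Committee's sealed list as backup, with the Committee disclosing only the line for that participant, since its copy is also a full list.

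**Cost.** One sealed envelope has to be moved and a few sentences changed. Because the copies have already been distributed and the section on protocol changes sends important changes to the ethics committee, a short amendment is needed. The practical downside is that the technician's box must be reachable whenever an emergency could arise. If the full protocol already contains a code break for a single participant, it is enough to state that route in place of the one described and to withdraw the Head Investigator's copy.
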